#### Nutrition counseling

Following randomization, participants will receive two in-person and five phone nutrition counseling sessions with the intervention RD. Personalized emails with feedback will be sent after participants return the diet checklists every 4 weeks. Participants may contact the intervention RD at any time to receive additional support. A final in-person counseling session will be conducted at visit 4. Nutrition counseling will be based on the Self-Determination Theory and use the Motivational Interviewing (MI) communication approach [39–43]. The dietitians providing the intervention will be screened for MI aptitudes prior to being hired, and they will receive training in this area prior to study initiation. The dietitian will also receive ongoing consultative support throughout the study from an RD who is a member of the Motivational Interviewing Network of Trainers (MINT). A lesson plan was developed to guide the counseling session for each in-person study visit. Participants will be asked to consent to being audio recorded during in-person nutrition counseling sessions at visits 2 and 3. The visit 2 audio recordings will be reviewed by the MINT RD to verify fidelity to the study diet guidelines, which consist of explaining the recommended and not recommended foods for the intervention diet and rationale for key dietary components. The MINT RD will review all visit 2 audio recordings and 20% of visit 3 audio recordings using the OnePass instrument [44] to assess use of the MI approach. A mean OnePass score ≥ 4 indicates average competence in MI.

### Measures

The SPMSQ will be used at screening to assess organic brain deficit. Personal information will be collected at visit 1. A medication audit, health history, vital signs, and blood biomarkers (insulin, glucose, hemoglobin A1c, lipids including high-density lipoprotein, vitamin K, vitamin D, calcium, vitamin B_12_, folate, homocysteine, Cardio IQ® [Omega-3 (EPA + DHA) index, omega-6/omega-3 ratio, EPA/arachidonic acid ratio, arachidonic acid, EPA, and DHA]) will be collected at each visit. Table 3 summarizes the primary and secondary outcome measures.

*Perceived fatigue will be assessed with the following scales:*
The FSS [45]: a nine-item questionnaire measuring the severity of perceived fatigue and its effect on daily activities. Scores range from 0 to 7, with higher scores indicating greater perceived fatigue severity. Obtaining scores every 4 weeks will provide more assessment points for the primary outcome measure and will improve the statistical power for hypothesis testing.Modified Fatigue Impact Scale (MFIS) [46], a 21-item assessment of the effects of fatigue related to physical, cognitive, and psychosocial functioning.Fatigue Scale for Motor and Cognitive Functions (FSMCF), a 20-item measure of cognitive and motor fatigue for people with MS.

*Motor function (gait and hand) will be assessed with the following tests:*
T25FW, a timed 25-ft walk to quantify mobility and leg function6MWT assesses distance walked in 6 minutes as a submaximal test of aerobic capacity.9HPT is a quantitative test of upper extremity function (hand) in which patients are timed as they put nine pegs into holes in a block and then remove them one at a time. The test is conducted twice with the nondominant hand and twice with the dominant hand.

*Cognitive function will be assessed by:*
SDMT-O is a screening tool for organic cerebral dysfunction.Perceived Deficits Questionnaire (PDQ) is a self-report measure of cognitive dysfunction specifically for MS.

*QOL will be assessed by:*
MSQOL54 [47] is a multidimensional health-related QOL measure that includes both generic and MS-specific items.SF-36 is a generic measure of health-related QOL.HADS [48] is an instrument used to assess mood and detect states of depression and anxiety.Mental Health Inventory (MHI) [49] provides an assessment of anxiety, depression, behavioral control, positive affect, and general distress.Multiple Sclerosis Impact Scale version 2 (MSIS v2) is a 29-item self-report measure of the impact of MS on day-to-day activities, including both physical and psychosocial aspects.Perceived Stress Scale 10 (PSS-10) [50] measures the degree to which situations in one’s life are perceived as stressful.

*Physical activity and sleep will be assessed by:*
Accelerometers (GT9X Link; ActiGraph, Pensacola, FL, USA) will be worn on the nondominant wrist during the 7-day food-recording period (including sleep time). Outcomes measured by accelerometer will include daily steps, time spent in light-intensity activity, time spent in moderate-intensity activity, time spent sedentary, sleep time, and sleep efficiency.International Physical Activity Questionnaire Long, (IPAQ-L) [51], a physical activity assessment.Pittsburgh Sleep Quality Index (PSQI) [52], a 19-item self-report sleep quality assessment.

*Diet quality will be assessed by:*
Three-day weighed food records to assess nutrient intake. Nutrient intake will be calculated using the most current version of the Nutrition Data System for Research software (Nutrition Coordinating Center, University of Minnesota, Minneapolis, MN, USA). (*Note*: Initially, 7-day records were collected. Based on participant feedback, and confirmed with the Minnesota Nutrition Coordinating Center, consecutive 3-day records are in used in a standard manner to assess nutrient intake [53–55].)Harvard Food Frequency Questionnaire (FFQ) is used to obtain information regarding the frequency and portion size of food and beverages consumed over the past year (visit 1) and the past 12 weeks (visits 2–4).

*Social support for eating will be assessed with:*
A version of Social Support for Eating Habits Scale [56], modified to include factors that are key to adherence by family members and friends, will assess social support for eating. These factors were identified in qualitative interviews with participants from our multimodal pilot study [4]. They include food purchasing, meal preparation, snack availability, and modeling study diet adherence while in the presence of the study participant.

To further monitor the health of participants, the following data variables will be collected:Health Practices Survey, a subset of questions asking about use of complementary therapies, including massage, meditation, yoga, and Tai Chi derived from the complementary health approaches section of National Health Interview Survey [57].Side effects questionnaire to assess new or worsening symptoms that might be attributed to diet or supplement changes (*see* Additional file 2: Appendix 1).“Your Eating Experience” questionnaire, developed by our research team to collect the following information: how often foods that are to be avoided were consumed during the past 4 weeks, what made it difficult to avoid those foods, and the factors that helped the participant follow the dietary guidelines (*see* Additional file 3: Appendix 2).

### Assessments and visit schedule

#### Visit 1 – week 1

Participants will fast for 12 hours prior to visit 1. Eligibility criteria will be checked, and the participant will be consented (Additional file 4: Appendix 3). Height and weight will be measured to confirm a BMI ≥ 19. If participants qualify for the study, their vital signs will be measured, and fasting blood will be drawn. Questionnaires including a medication audit and motor and cognitive testing will be completed, as listed in Fig. 2, and personal information such as duration of MS and handedness will be recorded. Participants will be instructed on how to (1) keep a 3-day food record and use a loaned food scale for weighing the amount of food eaten, (2) complete an FFQ, and (3) wear an accelerometer.

Participants will complete questionnaires, as listed in Fig. 2, via a secure Research Electronic Data Capture (REDCap) system at home 1–3 days after the study visit. Participants will wear an accelerometer for 7 continuous days (24 h/d) following this visit and record the foods, beverages, and dietary supplements consumed between Thursday and Saturday following visit 1. The accelerometer and dietary forms will be returned by mail.

#### Visit 2 – week 12

Participants will wear an accelerometer for the 7 days prior to visit 2 and will record the foods, beverages, and dietary supplements consumed between Thursday and Saturday prior to the visit. Participants will complete questionnaires (as outlined in Fig. 2) 1–3 days prior to visit 2 using REDCap. Participants will fast for 12 hours prior to visit 2. Vital signs, blood, motor and cognitive tests, and questionnaires will be completed at visit 2 (*see* Fig. 2). Food records, FFQs, and accelerometer data, will be reviewed for completeness. Participants will be randomized to one of the study diets.

The study participant and their family member(s) or adult companion will meet with an RD who will provide individualized nutrition counseling on the participant’s assigned study diet. The family/adult companion will be advised that, during our previous studies, we have observed that the study participants who have had their families adopt the study diet along with the study participants have had greater levels of success with adopting and sustaining the intervention diets. The family/adult companion will be advised that they are expected to be supportive of eating study-compliant foods.

Participants will view a brief video (< 20 min) that provides background information about the study diet to which they were randomized. Participants will receive an intervention food guide developed by study staff that describes their study diet, as well as *The Multiple Sclerosis Diet Book* [58] (low saturated fat diet) or *The Wahls Protocol* [59] (modified Paleolithic diet), both of which contain sample menus and recipes to assist with meal planning. Additional materials, such as grocery lists, will be provided to assist with diet adoption. A diet checklist that offers guidance to the participant in the form of prompts to eat the foods that are recommended and to avoid those that are not recommended will be provided. The participants and their adult companions will be given a study-adherent meal and practice recording the meal in the diet checklist to facilitate the learning of the principles of the assigned study diet and how to use the daily diet checklist.

Participants will be given a set of diet checklists to complete daily and a 3-day weighed food record booklet as well as an FFQ to complete prior to their next study visit. A self-addressed, stamped envelope will be provided so that participants can return their diet checklists at weeks 16 and 20 for the study dietitian to review. Upon receiving the week 20 checklist, the RD will send an email to acknowledge receipt and provide assessment comments. Participants will be asked to continue their usual physical activity, medication, and stress reduction regimens during the next 24 weeks unless their physician or physical therapist recommends changes.

The study RD will continue to coach the participant via coaching calls 2–3 days after visit 2 and then weekly for 3 weeks. A final coaching call will be made after receipt of the first 4-week diet checklist booklet.

#### Visit 3 – week 24

Participants will wear an accelerometer for the 7 days prior to visit 3 and will record the foods, beverages, and dietary supplements consumed between Thursday and Saturday prior to the visit. Participants will again complete questionnaires (as outlined in Fig. 2) 1–3 days prior to visit 3 using REDCap [60]. Participants will fast for 12 hours prior to visit 3. Vital signs, blood, motor and cognitive tests, and questionnaires will be completed at visit 3 (*see* Fig. 2). Food records, FFQs, and accelerometer data will be reviewed for completeness. The participant will meet with the study dietitian, who will review the diet checklists and answer questions. For participants randomized to the modified Paleolithic diet, the RD will encourage but not require the participant to reintroduce nightshades to the diet. If the participant elects to reintroduce nightshades, one nightshade food will be introduced on 1 day using this process: consume one bite of the food and wait 3 hours; consume ½ cup and wait 3 hours; consume 1 cup of food and wait 6 days. Symptoms will be recorded for a total of 7 days. If no symptoms have appeared by the end of 7 days, the food may be added back to the diet, and another food can be tested.

Participants will be given a fresh set of diet checklists to complete daily and a 3-day weighed food record booklet and FFQ to complete prior to their next study visit. A self-addressed, stamped envelope will be provided so that participants can return their diet checklists at weeks 28 and 32 for the study RD to review. An email will be sent to acknowledge receipt and provide assessment comments. The RD will not make coaching calls during this time, but study participants may contact the RD to request support. Participants will be reminded to continue their usual physical activity, medication, supplement, and stress reduction regimens during the next 12 weeks unless their physician or physical therapist directs them to make changes.

#### Visit 4 – week 36

Participants will wear an accelerometer for the 7 days prior to visit 4 and will record the foods, beverages, and dietary supplements consumed between Thursday and Saturday prior to the visit. Participants will again complete some questionnaires (as outlined in Fig. 2) 1–3 days prior to visit 4 using REDCap. Participants will fast for 12 hours prior to visit 4. Vital signs, blood, motor and cognitive tests, and questionnaires will be completed at visit 4 (*see* Fig. 2). Food records, FFQs, and accelerometer data will be reviewed for completeness. Participants will view two videos from the principal investigator: a thank-you video and an educational video about environmental factors that contribute to health. The participant will then meet with the study RD, who will review the diet checklists and answer questions.

### Risks and safety monitoring during intervention

#### Weight monitoring

If a participant’s BMI at visit 1 is < 19 kg/m^2^, they are ineligible for the study. If BMI at visit 2 or 3 is < 18.5 kg/m^2^, the participants will be asked to weigh themselves at home 1 and 2 weeks after the study visit (in the morning after their first void wearing street clothing) and report that information to the study coordinator/study team. If the BMI remains < 18.5 kg/m^2^ for 2 consecutive weeks:The intervention dietitian will conduct a special telephone coaching call to discuss strategies for increasing their calorie intake. The dietitian will make a second telephone call 1 week after the first call to provide continued support. Additional calls will be based on participant need and dietitian assessment. The participant will be instructed to continue weighing themselves weekly and reporting that information to the study team.The participant will be advised to follow up with their personal physician regarding the weight loss.

If the BMI increases to 19 kg/m^2^, the weekly weight monitoring will be discontinued. If a participant’s BMI at study visit 2 is 18.5–19 kg/m^2^, the participant may be at risk for additional weight loss, so the dietitian will alert them of this possibility and briefly discuss strategies to prevent weight loss.

The study team will report to the Data and Safety Monitoring Board (DSMB) the number of participants currently being monitored for low BMI and the corrective actions taken by study staff. The DSMB will review the BMIs of all participants quarterly along with any corrective action taken by study staff. The DSMB is constituted and managed by the NMSS and will review the adverse events, significant adverse events, and laboratory values greater than 10% outside the reference range. In addition to the quarterly reports provided to the DSMB, trial auditing procedures will also include a closed report from the study statistician with more details related to diet assignment and adverse events. The data management application also provides data manipulation and user activity audit trails. A medical monitoring board composed of two UI faculty physicians will receive all adverse events sheets. A data monitoring committee has not been constituted. Guidelines for stopping participation due to adverse events, patient decision to withdraw, or treatment medical provider recommendation have been established. Coaching and contact with study dietitian and motivational interviewing. Subjects who elect or are obligated to discontinue the study diet will be asked to complete the study forms and the motor assessments through 36 weeks.

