### Study Design

This 36-week randomized parallel group clinical trial consists of three 12-week periods during which assessments of perceived fatigue, quality of life, motor and cognitive function, physical activity and sleep, diet quality, and social support for eating will be collected. The 12-week periods will consist of:*Observation*: Participants continue eating their usual diet.*Intervention*: Participants will be randomized to either the modified Paleolithic or low saturated fat diet for the intervention period. Participants will receive support by a registered dietitian (RD) through coaching telephone calls and emails.*Follow-up*: Participants will continue the study diet for an additional 12 weeks with minimal RD support to assess the ability of the participant to sustain the study diet on their own.

Study evaluations will be done to compare the effects of the two study diets on perceived fatigue (primary outcome measured by FSS) and secondary outcomes (cognitive function, motor function, QOL). The protocol was prepared according to the Standard Protocol Items: Recommendations for Interventional Trials (SPIRIT) guidelines (*see* Figs. 1 and 2 and Additional file 1: SPIRIT Checklist).

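### The BMI 18.5–19 weight-loss alert applies only at visit 2, before the diet starts, and is not repeated at visit 3, before 12 more weeks of diet without coaching calls

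*Protocol article*

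**What the plan says.** Weight monitoring, under Risks and safety monitoring during intervention, sets the BMI rules by visit.

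- **Visit 1:** BMI below 19 kg/m² makes a person ineligible. The Visit 1 text agrees: "Height and weight will be measured to confirm a BMI ≥ 19".
- **Below 18.5:** the rule opens with "If BMI at visit 2 or 3 is < 18.5 kg/m^2". It leads to home weighing and, if the low value persists for two weeks, to dietitian calls and advice to see the personal physician. Weekly weighing stops once BMI is back up to 19.
- **18.5 to 19:** the rule reads "BMI at study visit 2 is 18.5–19 kg/m^2^, the participant may be at risk for additional weight loss". The dietitian then warns the participant and briefly discusses how to avoid losing weight. Visit 3 is not named.

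Study Design gives the timing. Before visit 2, "Participants continue eating their usual diet". At visit 2, "Participants will be randomized to one of the study diets". After visit 3, "Participants will continue the study diet for an additional 12 weeks with minimal RD support". The Visit 3 text adds: "The RD will not make coaching calls during this time, but study participants may contact the RD to request support".

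**The concern.** The alert exists because a person in this band may go on to lose more weight. At visit 2 that is a forecast about a diet not yet begun. At visit 3 the participant has had 12 weeks on the diet and faces 12 more, so the same reason holds at least as well. Entry requires a BMI of at least 19, so someone below 19 at visit 2 came down on their usual diet. Someone who first drops below 19 at visit 3 came down on the study diet. The first person gets the warning and the second does not.

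Weight loss on these diets is foreseeable from the article's own Background. It reports lower weight and BMI on a vegetarian version of the Swank diet, and greater weight loss on a Paleolithic diet than on its control diet. Those study populations differ from this one, so this shows only that the risk is plausible.

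What is at stake is a small piece of participant safety. The primary outcome, the power calculation and the analysis are not touched.

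**Working it through.** The plan gives no figure to reproduce. The check sets the rules against the visit schedule and then sizes the band.

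**Rules by visit**

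| Visit | Diet in the preceding 12 weeks | BMI < 18.5 | BMI 18.5–19 | Coaching calls scheduled afterwards |
|---|---|---|---|---|
| 2 (week 12) | usual diet | home weighing | alert and brief advice | five |
| 3 (week 24) | study diet | home weighing | none stated | none |

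The five calls are one 2–3 days after visit 2, three weekly calls, and one after the first checklist booklet. BMI must be available at visit 3, because the below-18.5 rule depends on it.

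**Is the band treated as a concern later in the trial?** Yes. Weekly weighing for a confirmed low BMI ends only at 19. A participant confirmed below 18.5 after visit 3 who recovers to 18.7 is still weighed weekly. One who has fallen to 18.7 at visit 3 has no stated action.

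**Size of the band.** Thresholds come from Weight monitoring. Visit 2 BMIs, the visit 3 value of 18.75 and heights are assumptions, because the article gives no BMI distribution.

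- Width: (19 − 18.5)/19 = 2.6% of body weight.
- Loss between visits 2 and 3 that puts a participant in the band:
  - from 19.5: 0.5/19.5 = 2.6% to 1.0/19.5 = 5.1%
  - from 20.0: 1.0/20 = 5.0% to 1.5/20 = 7.5%
- Further loss from mid-band to 18.5: 0.25/18.75 = 1.3%. In kilograms this is 0.25 × height²:
  - 1.55 m: 0.25 × 2.4025 = 0.60 kg
  - 1.65 m: 0.25 × 2.7225 = 0.68 kg
  - 1.85 m: 0.25 × 3.4225 = 0.86 kg
- Share of the visit 2–3 rate of loss that reaches 18.5 by visit 4. The two periods are both 12 weeks, so the share is (18.75 − 18.5)/(visit 2 BMI − 18.75):
  - visit 2 BMI 19.25: 0.25/0.50 = 50%
  - visit 2 BMI 19.5: 0.25/0.75 = 33%
  - visit 2 BMI 20.0: 0.25/1.25 = 20%

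Under these assumptions, a participant who reaches mid-band at visit 3 crosses 18.5 by visit 4 even if the loss slows to between half and a fifth of its earlier rate.

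**Other cover.** None of the following is stated to give the 18.5–19 alert after visit 2:

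- the visit 3 meeting: "The participant will meet with the study dietitian, who will review the diet checklists and answer questions"
- checklist emails and dietitian contact on request
- the side-effects questionnaire
- quarterly review of all BMIs by the DSMB

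**The case against.** The two rules may differ in scope on purpose. The below-18.5 rule is the real safety action and covers both visits. The 18.5–19 alert is a short caution tied to starting a diet, and visit 2 is where that happens. On this view nothing in the section contradicts itself, and a repeat at visit 3 is only a preference.

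Nutrition counseling also treats visit 3 as an in-person counseling session with its own lesson plan, which is not shown. Weight advice could sit there. The proposed change would not detect anyone who falls below 18.5 after visit 3, because it adds no weighing. It would amend a running trial with 58 people already consented, and the extra advice could fall more on one arm just before a period meant to test the diet with little support.

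Several of these points stand. The visit 2 alert is sensible and should stay, the fix adds advice and not detection, and the consequence is small. They do not close the gap. Each rule names its visits, so the narrower scope is written into the plan and is not just lost in condensing it. The lesson plan is not stated to contain the alert. The possible imbalance in advice already exists under the below-18.5 rule, which allows repeated dietitian calls after visit 3 and so intrudes more on the minimal-support period than a brief talk at an existing meeting.

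**Conclusion.** The concern holds and is minor. As written, the warning reaches people in the band when the diet starts and misses those who first enter it after 12 weeks on the diet. That reading rests on the text alone. The size rests on assumed heights and BMIs: the band is 2.6% of body weight, and from its middle a loss of about 0.6 to 0.9 kg leads below it. The number of participants affected cannot be estimated from the article and is probably small.

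**What to change.** In Weight monitoring, extend the 18.5–19 condition from study visit 2 to study visit 2 or 3. The dietitian then gives the same warning and short discussion in the meeting already scheduled at visit 3. Leave the thresholds, the two-week home-weight confirmation and the visit 4 procedures as they are.

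The cost is two added words, made as an amendment while the trial is running, and a few minutes of dietitian time for each participant in the band. No contact is added during the follow-up period itself. The one downside is that, if weight loss differs between the diets, this advice will be given somewhat more often in one group.

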#### Research hypothesis 1a

After 12 weeks of the diet intervention, relative to the observation period, at least 15% of participants in the low saturated fat diet group will demonstrate decreased perceived fatigue (assessed by FSS score), 30% will have improvement in QOL mental health and physical health scores (mean score increase of > 5 points), 50% will demonstrate improved cognition (> 5% improvement in mean Symbol Digit Modalities Test–Oral [SDMT-O] score), and 30% will demonstrate improved motor function (> 5% improvement in mean distance of 6 Minute Walk Test [6MWT]). In the modified Paleolithic diet group, ≥ 60% of the participants will demonstrate decreased perceived fatigue, 70% will have improvement in QOL mental health and physical health score, 70% will demonstrate improved cognition, and 55% will demonstrate improved motor function.

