### Data analysis

All analyses will be completed by a masked statistician who will not have access to study diet assignment. Data analysis will include both intention-to-treat and per-protocol analytic methods. Data for this study will be analyzed using SAS® 9.4 software (SAS Institute, Cary, NC, USA). Statistical significance will be set at α ≤ 0.05. Descriptive statistics will be calculated for all variables at all data collection times. Outliers will be checked for accuracy and possible entry errors. Respondents who drop out of the study will be compared with those who complete the study so that differences in baseline characteristics that may affect the study results will be detected. Patterns of missing data (missing at random, not missing at random) will be investigated [61]. The analytic methods will account for the type of missing data. The distributions of continuous variables will be evaluated for normality and homogeneity of variance. Appropriate transformations will be applied as needed, and/or statistical analyses for nonnormal data will be performed. Collinearity among fixed effect variables will be examined.

Repeated-measures analyses will use generalized linear mixed models methods to test for within-group and between-group changes in both primary and secondary outcomes. Intraclass correlations for repeated measures within patients will be included in the model structure for analyses. Mixed models for both continuous and categorical outcomes will have both random and fixed effects. Fixed effects will include characteristics such age, sex, intervention group, time indicators, and group-by-time interactions. Intercepts and slopes may be considered as random effects.

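### The follow-up list for participants who stop the study diet omits SDMT-O, so its intention-to-treat analysis would lack off-diet values that could have been collected

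*Protocol article*

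**What the plan says.** The rule stands at the end of the Weight monitoring text, under Risks and safety monitoring during intervention. Of participants who come off the diet, by choice or by necessity, it says that they "will be asked to complete the study forms and the motor assessments through 36 weeks". It names two kinds of data, forms and motor assessments.

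Elsewhere the protocol article names three kinds. For week 24: "Vital signs, blood, motor and cognitive tests, and questionnaires will be completed at visit 3". For week 36: "Vital signs, blood, motor and cognitive tests, and questionnaires will be completed at visit 4". The visit 2 text has the same list. The Measures section puts T25FW, 6MWT and 9HPT under motor function. Under a separate cognitive heading it lists two instruments. On the first it says: "SDMT-O is a screening tool for organic cerebral dysfunction". The second is a questionnaire, described in these terms: "Perceived Deficits Questionnaire (PDQ) is a self-report measure of cognitive dysfunction specifically for MS".

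SDMT-O is secondary outcome 6 in Table 3 and the cognition measure in hypotheses 1a and 2b. Hypothesis 1a sets a responder target for it in the low saturated fat group, where "50% will demonstrate improved cognition". Hypothesis 3 carries the measures of 1a and 1b forward to 24 weeks of diet. On analysis sets, the Data analysis section says: "Data analysis will include both intention-to-treat and per-protocol analytic methods".

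**The concern.** SDMT-O is neither a form nor a motor assessment in the protocol's own classification. Staff who follow the discontinuation sentence as written would therefore bring a participant in for walking and peg tests and not give the oral cognitive test at the same visit.

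An intention-to-treat analysis is meant to compare the groups as randomised, including those who left the assigned diet. If SDMT-O stops when the diet stops, whether a value is missing depends on a post-randomisation event that the assigned diet can influence. The two diets restrict different foods, so the share who stop may differ between them. The between-diet contrast on SDMT-O would then depend on a modelling assumption about values that could have been observed.

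Hypothesis 3 is the most exposed. It asks whether week-12 changes are sustained in at least 80% of participants, and people who stop the diet are central to that question. If more than 20% of those counted had no week-36 SDMT-O, the target could be met only by imputing them or by leaving them out of the denominator.

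**Working it through.** **1. Which outcomes the discontinuation list covers**

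| Outcome | Category in the protocol | Named after stopping? |
|---|---|---|
| FSS (primary), MFIS, FSMCF, MSQOL-54, PDQ and other questionnaires | forms | yes |
| T25FW, 6MWT, 9HPT | motor | yes |
| SDMT-O | cognitive test | no |
| Accelerometer (outcome 11, also in hypothesis 2b) | device | no |
| Blood biomarkers (outcome 18) | blood | no |

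**2. Which SDMT-O values would be missing.** Cognitive testing takes place at visits 1 to 4. Randomisation is at visit 2 (week 12), so visit 3 (week 24) is 12 weeks after diet start and visit 4 (week 36) is 24 weeks after.

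- Stops before visit 3: weeks 24 and 36 missing. This touches hypotheses 1a, 1b, 2b and 3.
- Stops after visit 3: week 36 only. This touches hypothesis 3, the sustained-intervention outcome in Table 3, and the between-group contrast that Table 4 places at the last visit.
- Everyone keeps the values from visits 1 and 2.

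**3. The plan's own figures.** The cognition row of Table 4 is for PASAT, which SDMT-O replaces: difference 5.8, SDs 6.0 and 6.3, 34 per group, alpha 0.05 (sidedness not stated; two-sided assumed).

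- Pooled SD = sqrt((6.0² + 6.3²)/2) = 6.15.
- Standard error = 6.15 × sqrt(2/34) = 1.49.
- Power = Φ(5.8/1.49 − 1.96) = 0.97, against at least 0.90 stated.
- Within group: SD of change = 6.0 × sqrt(2 × (1 − 0.5)) = 6.0; power = Φ(4.2/(6.0/sqrt(34)) − 1.96) = 0.98.
- Recruitment: 45 × 0.75 = 33.75, about 34.

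The stated figures reproduce.

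**4. Illustrations only.** The documents give no diet-discontinuation rate. The rates below are assumptions, and the scale is PASAT's.

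*Precision.* Suppose a share of the 34 evaluable per group has stopped and lacks SDMT-O (normal approximation, difference still 5.8):

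| Share stopped | n per group | Power |
|---|---|---|
| 10% | 31 | 0.96 |
| 20% | 27 | 0.93 |
| 30% | 24 | 0.90 |
| 40% | 20 | 0.85 |

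*What is estimated.* Suppose the on-diet difference is 5.8, stoppers show no difference between diets, and the share s stopping is equal in both groups. The difference in all randomised participants is 5.8 × (1 − s): 5.2, 4.6 and 4.1 at s = 10%, 20% and 30%.

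*Unequal stopping.* Suppose 35% stop one diet and 15% the other, and stoppers score 3 to 6 points worse than those who continue. A comparison of observed values alone shifts by (0.35 − 0.15) × 3 = 0.6 to (0.35 − 0.15) × 6 = 1.2 points, or 10% to 21% of 5.8. This is below one standard error (1.49). A mixed model that uses earlier SDMT-O values could reduce it.

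**The case against.** The sentence does not say that only these data are collected, and it does not say that SDMT-O stops. It is one line in a condensed article, next to a sentence fragment, and the schedule figure is not available to settle it. Because the visits name motor and cognitive tests together, the word motor may be shorthand for the whole in-person battery. This stands as a limit: the gap is inferred from an omission. It does not remove the point, because the article states a rule here, and that rule leaves out a category that the article separates elsewhere.

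A reader might infer that the intention-to-treat analysis of cognition as a whole becomes an on-diet analysis. The documents do not support that. PDQ, secondary outcome 15, is a self-report form and continues. Those who stop after visit 3 already have the 12-week SDMT-O. The planned mixed models use each participant's available values, and the Data analysis section undertakes to examine missing-data patterns and choose methods to suit them. That helps, but it replaces obtainable observations with an assumption.

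A reader might also take the 25% attrition in the sample size section as the loss, about 11 of 45 per group (0.25 × 45 = 11.25), with a standard error about 15% larger (sqrt(45/34) = 1.15). That attrition is nowhere said to be diet discontinuation with continued attendance. Participants lost to the study lack SDMT-O under any wording, and 34 per group is already the planned evaluable number.

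Nor is SDMT-O the only outcome exposed: the accelerometer and blood measures are unlisted too.

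**Conclusion.** The point holds, limited to SDMT-O and the other unlisted measures. As written, the discontinuation rule does not request SDMT-O off diet. If staff follow it literally, the intention-to-treat analysis of SDMT-O rests on on-diet data and a missing-data assumption, and it may be biased if stopping differs between the diets. The primary outcome, the other questionnaires and the motor tests are not affected.

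The size is unknown, because it depends on how many stop, when, and how they differ from those who continue. The illustrations show that the issue is mainly which effect is estimated and whether it is biased: power stays near 0.90 or above up to an assumed 30% stopping. They rest on assumed rates and on PASAT figures. No stated figure for the cognition row is shown to be wrong. The change is still worth making, because values not collected cannot be recovered by any later analysis.

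**What to change.** In the discontinuation sentence, insert 'and cognitive (SDMT-O)' after the word motor, so that the test is requested through week 36. In the same place, state whether the accelerometer and blood measures also continue after stopping. In Data analysis, state that the intention-to-treat model for SDMT-O uses all values from randomised participants, on or off the diet.

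The cost is a few words in the protocol and one short oral test at a visit that the participant is already asked to attend for motor testing. Sample size and the primary analysis do not change. Recruitment has begun, so the change helps only assessments still to come; participants who have already stopped and missed an SDMT-O should be counted and reported.
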